## Pre-treatment evaluation

History and Physical Examination within eight weeks of study registration (No exceptions to timelines):Including prior cancer therapies, and cancer-specific concomitant medications.Chemotherapy and surgery within twelve weeks of RT start date (No exceptions to timeline).Pregnancy test for people of child-bearing potential within 4 weeks of RT start date (No exceptions to timeline).

## Interventions

*Standard Arm—Multiple Fraction PBI (Arm 1)*.

Participants on Arm 1 will be treated with PBI with a dose of 26 Gy in 5 daily fractions.*Experimental Arm—Single Fraction PBI (Arm 2)*.

Participants on Arm 2 will be treated with PBI with a dose of 13 Gy in 1 fraction.

### Immobilization

Immobilization and positioning must follow institutional guidelines. Use of angled versus flat breast boards must follow departmental practice; while flat positioning may be preferred for Volumetric Modulated Arc Therapy (VMAT) clearance, either approach is acceptable based on clinical and technical considerations. The participant will be positioned supine, with both arms (or only ipsilateral arm) over the head preferred, but positioning with both arms down is acceptable if needed. Non-supine positioning is permitted if clinically required, though expected to be uncommon.

### Imaging/Localization/Registration

All participants on both treatment arms will undergo CT simulation per the institution’s guidelines. Radio-opaque markers will be placed on the surgical scar. Markers may also be placed at the infraclavicular head and 2 cm inferior to the breast tissue and/or to delineate breast tissue. Wire localization may be used based on institutional preference but is not required. Other markers such as tattoos may also be used for daily localization and setup according to institutional guidelines. Axial CT images will be obtained, with the scan range according to institutional guidelines.

Deep inspiration breath hold (DIBH) may be used as per institutional guidelines.

Image guidance is required for treatment delivery, with imaging using either kV or cone-beam computed tomography (CBCT) permitted, depending on departmental practices.

For image guidance, relevant clips that are within or adjacent to the lumpectomy are contoured. Image-guided radiation therapy (IGRT) will be based on a clip match.

In the absence of clips, the seroma or an alternate surrogate (e.g., chestwall, scar wire) visible on kV or CBCT should be used.

For patients treated in the single-fraction arm, intrafraction imaging is suggested to verify or adjust patient positioning to correct for the increased risk of intrafraction motion.

All patients will have a day 1 post-treatment CBCT performed with the treated volume visible in the CBCT field of view, if technically feasible without any collisions. This CBCT will be saved within the ARIA system for retrospective analysis. CBCT acquisition parameters as per local departmental practice.

### Volume definitions

*Clinical Target Volume (CTV)*: Lumpectomy (as defined on CT simulation with the aid of surgical clips, if present) + 1.0–1.5 cm 3D expansion. The CTV will be limited posteriorly by the pectoral fascia and anteriorly by the skin surface, cropped to anatomical boundaries (lung, chest wall, ribs, sternum, muscles, etc.) and 0.5 cm below the skin surface per RO discretion.*Planning Target Volume (PTV)*: CTV + 0.7–1.0 cm 3D expansion (recommended margins may vary depending on physics guidelines considering setup, immobilization, and IGRT practices). 1.0 cm is recommended, particularly for DIBH, large or mobile breast, or lumpectomy > 15 cc (margin may be reduced in consultation with physics).*PTV_Eval*: PTV cropped back to 0.5 cm below the skin surface, and 0.5 cm from lung, but including any CTV within 0.5 cm of lung.

### Organs at risk (OAR) doses

Delineation of organs at risk (OARs) is required and must include the ipsilateral and contralateral lung, heart, and ipsilateral and contralateral breast. Constraints for OARs for the five-fraction regimen are based on provincial practice and protocols from other studies using a similar number of fractions such as the FAST-Forward and the Florence PBI trials [13, 20]. Constraints for single-fraction radiation were determined by calculating the corresponding EQD2 from the five-fraction regimen using an α/β value of 2, and then rounded or adjusted for conservativeness based on trial group consensus opinion. OAR dose constraints are listed in Table 1.

The “Ipsilateral breast-PTV” constraint is applied to the ipsilateral breast structure with the PTV subtracted. All OAR constraints are prioritized above PTV coverage and homogeneity metrics, except for contralateral breast D0.035 cc which is the lowest priority and should be exceeded if necessary to achieve all other constraints. All planning constraints (except contralateral breast) are mandatory trial requirements.

**Table 1 Tab1:** SHIFT-PB planning constraints

Mandatory Planning Constraints				
OAR	Fractions			
	5		1	
Ipsilateral lung	V10 Gy	≤ 20%	V5 Gy	≤ 20%
Heart	V7 Gy	≤ 5%	V4 Gy	≤ 5%
	V3 Gy	≤ 10%	V2 Gy	≤ 10%
	V1.5 Gy	≤ 30%	V1 Gy	≤ 30%
Contralateral lung	V5 Gy	≤ 10%	V3 Gy	≤ 10%
Ipsilateral breast-PTV	V50%	≤ 50 [60]%	V50%	≤ 50 [60]%
Target Planning Goals (both arms)				
PTV_eval	V95%		≥ 98 [95]%	
	V105%		≤ 5 [10]%	
Body	D0.035 cc		≤ 107 [110]%	
Non-Mandatory OAR Constraints (both arms)				
Contralateral breast	D0.035 cc		≤ 1 [2] Gy	

Acceptable values indicated in brackets where applicable

### Treatment planning

Planning must be performed using VMAT with a minimum of two partial arcs, as appropriate, to minimize entrance dose through contralateral tissues. The selection of beam energy is at the discretion of the treating department. Optimization must be performed to the fully expanded PTV (or surrogate opti structure) to ensure robust target coverage during treatment considering setup uncertainty and intrafraction motion. Use of temporary planning structures to ensure sufficient build-up to the fully expanded PTV for optimization is mandatory, though the exact method is not prescribed. Flash buildup as per departmental practice– with a recommended thickness of 0.5–1.0 cm to the PTV and a HU of -500– is an example. After optimization, these structures should be removed, and the dose recalculated without buildup, then evaluated on the PTV_eval.

### Target planning goals—both arms

The volume of the PTV_eval receiving 95% of the prescription dose should be ≥ 98% (preferred), or ≥ 95% (mandatory).

The maximum dose to 0.035 cc of any tissue should be ≤ 107% (preferred), or ≤ 110% (mandatory) of the prescription dose. Maximum dose should fall within the PTV.

The volume of the PTV_eval receiving ≥ 105% of the prescription dose should be ≤ 5% (preferred) or ≤ 10% (mandatory).

### Quality assurance (QA) (Arms 1 & 2)

In order to ensure participant safety and effective treatment delivery, a robust quality assurance protocol is incorporated. The following requirements must be completed for each participant:

Prior to treatment, each participant must be peer reviewed by a radiation oncologist with PBI expertise. Peer review of contours must occur before treatment. QA rounds are optional.All treatment plans must undergo physics QA checks per institutional practice.All PBI treatments must be delivered on a radiotherapy linac appropriate for VMAT PBI and compliant with a QA schedule as recommended by current international published guidelines. *As this study will only involve BC Cancer sites, formal credentialling of centres will not be required, as it is assumed that all treatments will be delivered on RT linacs appropriate for VMAT PBI and with QA schedule as recommended by guidelines.

Peer review of contours must be done within a treating centre and must follow institutional guidelines. As this is a BC Cancer-only trial, acceptable documentation includes use of the provincial ARIA platform. The completed peer review form can be printed and uploaded to REDCap for trial tracking purposes.

### Systemic therapy

Hormone therapy and targeted cancer drugs, such as trastuzumab (Herceptin), are permitted. The use of systemic therapy that are cytotoxic, immunotherapeutic, or molecularly targeted agents are not allowed within 2 weeks prior to radiation until 1 week after the last fraction. Investigational therapy is prohibited within 14 days prior to initiation of study treatment and during study treatment.

### Data handling and recordkeeping

All participant data for the study for the study must be recorded on printed or electronic case report forms (CRF), unless electronically transmitted to the sponsor or designee, with the investigator responsible for verifying accuracy by signing the CRF. Monitoring details describing strategy, methods, responsibilities and requirements, including handling of noncompliance issues and monitoring techniques (central, remote, or on-site monitoring) are provided in the SHIFT-PB Monitoring Plan. Study monitors will verify source data to ensure accuracy, participant safety, and compliance with protocols, International Council for Harmonization (ICH) Good Clinical Practice (GCP), and regulations.

### Patient discontinuation / withdrawal

A participant may voluntarily withdraw from the study at any time at his/her own request. Participants may also be withdrawn at any time at the discretion of the investigator if any exclusion/inclusion criteria have been violated during the study, they are unable to meet the mandatory planning requirements after enrollment, or for safety reasons, etc.

At the time of discontinuing from the study, if possible, an early discontinuation visit must be conducted. The clinical evaluations that would have been performed at the end of the study should be obtained. If a participant is removed because of an adverse or serious event, they should remain under medical observation as long as deemed appropriate by the treating physician and follow recording and reporting requirements.

Participants withdrawn or discontinued can be replaced at the discretion of the sponsor-investigator/Study Principal Investigator.

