## Exclusion criteria

### Participants are excluded from the study if any of the following criteria apply

History of non-breast malignancies except adequately treated non-melanoma skin cancers, in situ cancers treated by local excision or other cancers curatively treated with no evidence of disease for ≥ 5 years.Uncontrolled concurrent malignant cancer.Seroma not visible.Ipsilateral implanted cardiac device.Prior radiotherapy requiring summation for planning.Inability to meet mandatory planning constraints.Requirement for a radiation boost (as determined by treating investigator).Positive lymph nodes.Positive surgical margins defined as “ink on tumor” (any invasive or DCIS cells on ink).Surgical cavities lacking clear delineation (surgical clips are not required but may assist in target delineation).Known germline BRCA1/2 mutation.Serious medical comorbidities precluding radiotherapy (i.e., connective tissue disorders such as lupus or scleroderma).Pregnant or breastfeeding.

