### Follow-up evaluation and assessment of efficacy

After treatment, participants will be followed up after 2 weeks. Clinical follow-up appointments will then be scheduled at 2 months, 6 months, 12 months, 18 months, and 24 months, and may be conducted via telephone or videolink. Follow-up visits requiring a physical exam may still be conducted via telephone/videolink if the physical exam is performed within the specified window by the participant’s Family Practitioner (FP) or General Practitioner in Oncology (GPO), with documentation. Otherwise, the participant must return to the clinic for the physical exam to be performed on-site. At each visit, a medical history will be conducted by the oncologist, and CTCAE toxicities recorded using the adverse events form, as well as ECOG scores. The POSI-Breast questionnaire is to be completed at baseline and on each follow-up visit.

A mammogram will be done beginning 6 months after treatment, then annually thereafter. Cytological or histological confirmation of the ipsilateral and contralateral primary tumor is required, including at the time of recurrence.

There is no planned follow-up at the end of the study. Additional care or follow-up assessments that will be provided to participants after they complete or discontinue the study will involve standard of care treatment for what is normally expected for their condition.

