## Statistical considerations

### Randomization

This study will employ a 1:1 randomization between Arm 1 and Arm 2, with further stratification by centre. Permuted block randomization will be used to reduce selection bias, promote allocation concealment, and improve balance across groups over the trial period. Participants will be randomized based on computer-generated random permuted blocks using a block size based on a multiple of 2 (with the block size known only to statistician until analysis is completed). This is an open-label randomized controlled study design, however, outcome assessors and data analysts will be blinded to the identity of each treatment arm.

The Coordinating Centre will be responsible for randomization of participants using a randomization module in the REDCap Electronic Data Capture (EDC) system, which will be used for trial data collection. In conjunction with trial statistician and Site Principal Investigators, the Coordinating Centre will be responsible for storing and analyzing trial data.

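### Participants who fail the planning limits after enrolment may be withdrawn and replaced; if planning follows randomization, these are post-randomization exclusions with no scheduled post-treatment follow-up

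*Protocol article*

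**What the plan says.** Four parts of the protocol article bear on this.

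- **Eligibility.** The exclusion criteria include "Inability to meet mandatory planning constraints".
- **Withdrawal.** The section on patient discontinuation / withdrawal also foresees failure later on. The investigator may withdraw a participant if "they are unable to meet the mandatory planning requirements after enrollment". It then adds: "Participants withdrawn or discontinued can be replaced at the discretion of the sponsor-investigator/Study Principal Investigator". For follow-up it provides this: "At the time of discontinuing from the study, if possible, an early discontinuation visit must be conducted". The assessments due at the end of the study are to be obtained then. Continued observation is described only for people removed because of an adverse event.
- **Planning limits.** The section on organs at risk states: "All planning constraints (except contralateral breast) are mandatory trial requirements". Table 1 gives separate dose cut-offs for five fractions and for one fraction, with the same volume limit on each row. The single-fraction limits were derived from the five-fraction ones by EQD2 at an α/β of 2, then rounded or adjusted.
- **Design and follow-up.** On masking of treatment: "This is an open-label randomized controlled study design". Follow-up starts two weeks after treatment, and then: "Clinical follow-up appointments will then be scheduled at 2 months, 6 months, 12 months, 18 months, and 24 months".

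**The concern.** Withdrawal for planning failure is a discretionary decision made by someone who can know the arm, against limits that depend on the arm. If it happens after allocation, the participants who remain are no longer simply those who were randomized. Those removed also leave almost no outcome data, because the visit schedule runs from a treatment they did not receive on protocol. An analysis plan can keep such a person in the allocated arm, but it cannot supply toxicity, quality-of-life or recurrence data that were never collected.

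At stake are the secondary between-arm comparisons listed at the start of the Methods: toxicity, local control, quality of life, overall survival and progression-free survival. The two survival endpoints are timed from randomization, so a participant withdrawn at planning would be censored almost at once. By-arm planning failure is also useful feasibility information for the phase III trial that the Discussion foresees.

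**Working it through.** **1. The protocol's own EQD2 figures.** EQD2 = D(d + α/β)/(2 + α/β), where D is total dose and d is dose per fraction.

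- α/β 3.5: 26(5.2 + 3.5)/5.5 = 41.13 Gy; 13(13 + 3.5)/5.5 = 39.0 Gy.
- α/β 2: 26(5.2 + 2)/4 = 46.8 Gy; 13(13 + 2)/4 = 48.75 Gy.

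All four match the Background.

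**2. Table 1 limits relative to prescription.** Inputs are the Table 1 cut-offs and the prescriptions in the Interventions section (26 Gy and 13 Gy). If the target is the same and the dose distribution scales with prescription, cut-off divided by prescription measures how hard a limit is to meet. The EQD2 columns use α/β 2.

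| Mandatory limit | 5 fractions | 1 fraction | Ratio | EQD2, 5 fractions | EQD2, 1 fraction |
|---|---|---|---|---|---|
| Heart, ≤ 5% volume | 7/26 = 26.9% | 4/13 = 30.8% | 0.875 | 5.95 | 6.00 |
| Heart, ≤ 10% volume | 3/26 = 11.5% | 2/13 = 15.4% | 0.75 | 1.95 | 2.00 |
| Heart, ≤ 30% volume | 1.5/26 = 5.8% | 1/13 = 7.7% | 0.75 | 0.86 | 0.75 |
| Contralateral lung | 5/26 = 19.2% | 3/13 = 23.1% | 0.833 | 3.75 | 3.75 |
| Ipsilateral lung | 10/26 = 38.5% | 5/13 = 38.5% | 1.00 | 10.00 | 8.75 |
| Ipsilateral breast minus PTV | 50% | 50% | 1.00 | – | – |

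Four of six limits are tighter in Arm 1, two are equal and none is tighter in Arm 2. Doubled to the 26 Gy scale, the single-fraction heart limits are 8, 4 and 2 Gy and the contralateral lung limit is 6 Gy, against 7, 3, 1.5 and 5 Gy in Arm 1. Under the scaling assumption, the same relative plan can fail in Arm 1 and pass in Arm 2, but not the reverse. The PTV_eval and body goals are percentages common to both arms and add no difference.

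**3. When planning is judged.** The text does not say.

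- For planning after allocation: CT simulation is described under Interventions for participants on both arms; the pre-treatment evaluation lists no simulation or plan; arm-specific limits can be applied only once the arm is known, unless both plans are made; and the withdrawal section expects failures after enrolment.
- For planning before allocation: inability to meet the constraints is an exclusion criterion, next to a seroma that cannot be seen and a cavity that cannot be delineated; and the withdrawal section speaks of enrolment, not randomization.

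The first reading is the more natural one. Imaging before entry is not a completed plan.

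**4. What follow-up remains.** The scheduled visits are at 2 weeks and at 2, 6, 12, 18 and 24 months, six in all, counted from treatment. A plan is judged before delivery, so a participant withdrawn for planning failure has 0 of 6, plus at most one discontinuation visit.

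**5. Scale, under assumed counts.** The documents give no failure rate. With 60/2 = 30 per arm and k withdrawals in one arm, k/30 of that arm's event rate is unobserved: 0, 3.3, 6.7 or 10.0 percentage points for k = 0, 1, 2 or 3. If each is replaced in the same arm, the fraction is k/(30 + k): 0, 3.2, 6.3 or 9.1 points. These are worst-case widths for illustration, not expected bias, and nothing in the documents caps k at 3.

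**The case against.** The strongest reply is that the fault rests on a sequence that the article does not state. If every plan is judged before randomization, nobody is removed after allocation for this reason and the problem does not arise. That stands, and the point is conditional on it. It does not dispose of the matter, because the withdrawal rule itself provides for planning failure after enrolment.

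Second, a difference between arms needs a heart or contralateral lung limit to be the one that binds, and no document says which limit causes failures. If it is ipsilateral lung, ipsilateral breast or a target goal, Table 1 implies no difference. Target margins are also flexible ("recommended margins may vary depending on physics guidelines considering setup, immobilization, and IGRT practices"), so larger margins in Arm 2 could offset the tighter Arm 1 limits. Re-optimization, with organ limits ranked above coverage, and breath hold will rescue some plans. All of this stands. A reader might infer from the four-of-six count that Arm 1 will lose more participants, or that Table 1 is wrong. Neither is supported: in EQD2 the heart and contralateral lung limits nearly coincide, as the protocol intends.

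Third, the primary endpoint is accrual and randomization of 60, and toxicity, local control and quality of life are only described. This limits the consequence but does not remove it, since the Methods still set out to compare the arms on these outcomes.

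Fourth, withdrawal is discretionary, and the discontinuation visit is meant to capture the end-of-study assessments. Both are true. A visit held before any treatment, and only where possible, still carries no information on later toxicity or recurrence.

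**Conclusion.** The point holds in conditional form. If planning follows randomization, the withdrawal section as written permits post-randomization exclusion and replacement, by an investigator who can know the arm, of participants who then have no scheduled post-treatment follow-up. Their number could differ by arm if a heart or contralateral lung limit binds, given like target volumes and plans that scale with prescription.

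The size and direction of any bias in the secondary comparisons are unknown, and it is probably small. A reader might go further and infer that the feasibility result is compromised. It is not: withdrawal after randomization does not change the number accrued and randomized. The wording is still worth changing now, because follow-up that was not collected cannot be recovered later.

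**What to change.** Amend the section on patient discontinuation / withdrawal along these lines:

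> A randomized participant whose plan cannot meet the mandatory limits stops protocol treatment but remains in the study. Visits take place at 2 weeks and at 2, 6, 12, 18 and 24 months from the start of the radiotherapy actually given, or from randomization if none is given. The participant is analysed in the allocated arm and is not dropped from between-arm comparisons because a replacement was enrolled. Planning failures are reported by arm as feasibility data.

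The separate time anchor is needed because the present schedule runs from protocol treatment. The cost is one paragraph of wording and up to six visits per failure. A few participants treated outside the protocol limits will stay in the analysis and slightly dilute the regimen comparison.

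I would not require every plan to meet both columns of Table 1 before allocation. That would hold Arm 2 to the tighter Arm 1 limits and narrow eligibility, a trade-off that the likely size of the problem does not justify.

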### Follow-up evaluation and assessment of efficacy

After treatment, participants will be followed up after 2 weeks. Clinical follow-up appointments will then be scheduled at 2 months, 6 months, 12 months, 18 months, and 24 months, and may be conducted via telephone or videolink. Follow-up visits requiring a physical exam may still be conducted via telephone/videolink if the physical exam is performed within the specified window by the participant’s Family Practitioner (FP) or General Practitioner in Oncology (GPO), with documentation. Otherwise, the participant must return to the clinic for the physical exam to be performed on-site. At each visit, a medical history will be conducted by the oncologist, and CTCAE toxicities recorded using the adverse events form, as well as ECOG scores. The POSI-Breast questionnaire is to be completed at baseline and on each follow-up visit.

A mammogram will be done beginning 6 months after treatment, then annually thereafter. Cytological or histological confirmation of the ipsilateral and contralateral primary tumor is required, including at the time of recurrence.

There is no planned follow-up at the end of the study. Additional care or follow-up assessments that will be provided to participants after they complete or discontinue the study will involve standard of care treatment for what is normally expected for their condition.

